## Abstract

**Background:**

Postoperative pain is common in the intensive care unit despite the administration of analgesia. Some trials suggest that massage can be effective at reducing postoperative pain in acute care units; however, its effects on pain relief in the intensive care unit and when pain severity is highest remain unknown.

**Objective:**

The objective is to evaluate the effectiveness of hand massage on the pain intensity (primary outcome), unpleasantness and interference, muscle tension, anxiety, and vital signs of critically ill patients after cardiac surgery.

**Methods:**

A 3-arm randomized controlled trial will be conducted. A total of 79 patients who are 18 years or older, able to speak French or English and self-report symptoms, have undergone elective cardiac surgery, and do not have a high risk of postoperative complications and contraindications to hand massage will be recruited. They will be randomly allocated (1:1:1) to standard care plus either 3 20-minute hand massages (experimental), 3 20-minute hand holdings (active control), or 3 20-minute rest periods (passive control). Pain intensity, unpleasantness, anxiety, muscle tension, and vital signs will be evaluated before, immediately after, and 30 minutes later for each intervention administered within 24 hours postoperatively. Peer-reviewed competitive funding was received from the Quebec Nursing Intervention Research Network and McGill University in December 2015, and research ethics approval was obtained February 2016.

**Results:**

Recruitment started in April 2016, and data collection is expected to be complete by January 2017. To date, 24 patients were randomized and had data collection done.

**Conclusions:**

This study will be one of the first randomized controlled trials to examine the effect of hand massage on the pain levels of critically ill patients after cardiac surgery and to provide empirical evidence for the use of massage among this population.

**ClinicalTrial:**

ClinicalTrials.gov NCT02679534; https://clinicaltrials.gov/ct2/show/NCT02679534 (Archived by WebCite at http://www.webcitation.org/6l8Ly5eHS)

## Introduction

### Overview

Undergoing cardiac surgery constitutes a major event for patients that is accompanied by physical and psychological symptoms such as postoperative pain [1-5] and anxiety [6-8]. Recent studies reveal that massage could complement pharmacological treatments and have positive effects in reducing these symptoms in acute care units [9-11], yet empirical evidence is lacking to support the same effects early in the postoperative phase when patients are in the intensive care unit (ICU) and pain is at its highest.

In the ICU, postoperative pain can be compounded by routine ICU procedures such as turning, coughing, breathing, and chest tube removal, activities which are perceived to be the most painful in the immediate postoperative period [3,5]. Given the higher severity and complexity of pain in the ICU, findings from massage studies conducted on acute care wards cannot be extrapolated to the unique context of the ICU and the early recovery phase after cardiac surgery. Further evidence is needed to unravel the potential role of massage in relieving the pain of cardiac surgery in ICU patients and guide international clinical practice guidelines with regard to the use of this complementary nonpharmacological intervention in this patient population.

### Background

Cardiac surgeries, such as coronary artery bypass grafting and valve replacement, rank among the most frequently performed surgical interventions worldwide [12] and necessitate the routine admission of patients to the ICU. Cardiac surgeries are commonly indicated to reduce anginal pain, but the surgical procedure itself can lead to the development of postoperative pain. Mounting evidence shows that cardiac surgery ICU patients experience moderate-to-severe pain reaching proportions as high as 74% despite the use of analgesics [2-5], with the highest pain intensity commonly experienced in the first 24 hours postsurgery [13].

Unrelieved postoperative pain can interfere with patients’ ability to cough and mobilize effectively, which predisposes them to postoperative complications such as atelectasis, pneumonia, and deep vein thrombosis [2,5,14], thereby delaying recovery and ICU discharge. Moreover, the intensity of acute postoperative pain immediately after surgery is a significant predictor of the presence and severity of persistent postoperative pain up to 2 years postsurgery [15-17], a serious and often unrecognized complication after cardiac surgery that may interfere with daily activities and quality of life [18].

Among the pharmacological approaches to pain control, opioids constitute the mainstay of treatment in the ICU [19,20], yet pain has been shown to persist even during unrestricted use of these analgesic agents [13,21]. The use of complementary nonpharmacologic interventions such as massage has been suggested in the clinical practice guidelines of the Society of Critical Care Medicine given their opioid-sparing and analgesia-enhancing potential [20]. Massage has been defined as the manual manipulation of muscles and soft tissues of the body through the application of various systematic and rhythmic hand movements [22,23].

A recent systematic review exploring the effectiveness of massage on postoperative outcomes among patients undergoing cardiac surgery [24] indicated that out of the 7 eligible studies (N=40-252/study), 6 reported that massage therapy ranging from 20 to 30 minutes in duration improved postoperative outcomes such as pain, anxiety, and muscle tension [9,10,25-28], while only one study reported no positive results [29]. The latter study evaluated the effectiveness of a 30-minute massage therapy involving each limb for 5 minutes followed by a 10-minute back massage while patients were lying on the left side. The positioning required for the back massage might have obscured or minimized the potential benefit of massage in relieving pain, anxiety, and muscle tension given that side-lying may exert traction on the sternotomy site, causing pain [3] and increasing muscle tension and possibly anxiety as turning on one side could be perceived as a painful procedure. Of note, only one of these studies was conducted in the ICU [25], and it lacked random assignment.

One pilot randomized controlled trial (RCT) conducted with 40 ICU patients post–cardiac surgery [30] showed promising pain relief and muscle relaxant effects of up to 3 15-minute hand massages, whereas the administration of a single massage therapy did not yield any significant decrease in pain intensity or muscle tension, suggesting that repeated administration of hand massage is necessary in this patient population.

Overall, there is a paucity of high-level evidence on which to base massage therapy decisions in the management of pain in post–cardiac surgery ICU patients. Extrapolations of evidence from other patient populations and clinical settings are flawed by the differing health status and symptom severity of this specific subgroup of ICU patients. Future rigorous RCTs conducted in the context of the ICU and with cardiac surgery adults in their immediate postoperative period are essential to make recommendations for the use of massage in clinical practice including the minimal effective dose, body area massaged, and techniques employed.

**Figure 1 figure1:**
[figure not shown]
Adapted diagram of the neuromatrix theory of pain.

Eligibility criteria.Inclusion criteria:18 years of age and olderAble to speak French or EnglishElective cardiac surgeryAble to answer questions and self-report symptomsExclusion criteria:Previous cardiac surgeryDiagnosis of cognitive or psychiatric disorderPulmonary artery pressure >50 mm HgRight ventricular failureSystolic left ventricular dysfunction (ejection fraction 35% or less)Body mass index >30 kg/m^2^Prolonged bleeding from the chest drainage tubes (>200 mL/h)Having mechanical blood pressure support (eg, intra-aortic balloon pump)Receiving cardiac pacing with complete control of heart ratePeripheral intravenous line in the handsSuppurating/infective/inflammatory skin condition of the handsHypersensitivity to touch

### Theoretical Framework

The protocol is based on the neuromatrix theory of pain [31] where the brain’s neural network, the body-self neuromatrix, integrates multiple inputs such as sensory (eg, cutaneous) and opioid systems (ie, endogenous opioids) to influence the sensory (intensity, localization, and quality), affective (unpleasantness), and cognitive dimensions (interference with daily functioning) of pain (Figure 1). The sensory stimulation of nonnociceptive fibers in the skin and muscles involved in massage could block the transmission of nociceptive impulses in the dorsal horns and may increase the release of beta-endorphins in the bloodstream [32,33], which block the release of neurotransmitters from the nociceptive fibers (especially substance P) [34], thereby blocking the transmission of nociceptive impulses from reaching the body-self neuromatrix where pain perception occurs. Similarly, by blocking the transmission of nociceptive signals, the stimulation of the stress-regulation system responsible for the activation of the noradrenergic and sympathetic nervous system could be inhibited. The resultant lack of up-regulation of adrenaline and noradrenaline could explain the potential effects of massage in decreasing blood pressure, heart and respiratory rates, and the subjective sensations of anxiety [35-37].

### Aim

The primary aim of this research study is to compare the effect of 3 20-minute hand massage administrations by a trained nurse within 24 hours after cardiac surgery versus hand-holding (ie, simple touch) and standard care on the postoperative pain intensity of adult ICU patients.

## Methods

### Trial Design

This research study is designed as a randomized, controlled, patient-blinded, single-center superiority trial with 3 parallel groups and a 1:1:1 allocation ratio. A modified Consolidated Standards of Reporting Trials flow diagram for individual RCTs of nonpharmacologic treatments will be used to document recruitment and retention of participants (see Multimedia Appendix 1) [43].

### Participants

This RCT targets adults admitted to the ICU after undergoing cardiac surgery in a university-affiliated hospital in Canada. A single setting was selected for this study because of standardized pain management practices and surgical techniques and single patient rooms. Patients will be screened for inclusion using the eligibility criteria seen in Textbox 1. Patients at higher risk of postoperative complications and those with contradictions to having their hands massaged will be excluded.

### Sample Size and Sampling Procedure

A power analysis was conducted using the G*Power 3 program [38] to estimate the sample size required to capture the potential effects of massage to decrease the primary outcome (pain intensity) and to strengthen the statistical conclusion validity. The mean treatment difference was observed to be greater than 1.5 in several RCTs [11,26,39,40] and approximates the clinically significant difference of 2 points on the 0 to 10 Numeric Rating Scale (NRS) [41]. This trial is powered to be able to detect a difference in the pain intensity score of 1.5 between the hand massage and standard care group. The standard deviation of pain intensity scores is approximately a 2.0 value, which was selected for the sample size calculation. To detect a mean difference in pain intensity scores of 1.5 points (SD 2.0) immediately after the third massage with a 2-sided significance level of .05 and power of .80 with equal allocation to 3 arms and a repeated measures between factors context with 3 measurements would require a minimum of 72 patients.

Given the low attrition rates observed with this patient population (0% [9,10,30] and 35/287 (12.2%) [29]), a 10% drop-out rate is considered in the calculation of the total sample size. Therefore, the final size required for this RCT is 79, and it will be reached using convenience sampling.

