### Data Analysis

The data will be entered in the SPSS software version 22.0 (IBM Corp), and a random subset of data will be used to identify missing or erroneous values. This study aims to use intention-to-treat analysis by including every participant who has been randomized, regardless of group assignment, study withdrawal, or protocol deviations.

Descriptive statistics will be calculated for sociodemographic and medical-surgical data and the baseline scores on all the outcome variables. Group differentiation in sociodemographic and medical-surgical characteristics for participant patients will be investigated using chi-square tests of independence for nominal level variables and one-way analyses of variance (ANOVA) for interval and ratio level variables. If group differences exist, the respective variable will be included as a covariate in the subsequent analyses. Frequencies and percentages of the location and descriptors of pain (ie, sensory dimension of pain) will be calculated for each group and assessment point and used to describe the pain characteristics of participants. Data on pain location and quality will be compared over time.

Repeated measures between ANOVA factors will be used to test for treatment (hand massage, hand-holding, rest), time (before, immediately after, and 30 minutes later), and interaction effect for pain intensity, pain unpleasantness, muscle tension, anxiety, and means of vital signs. This will be run for each intervention and each of these outcome variables. One ANOVA test will be performed for pain interference with the independent variable being group assignment (hand massage, hand-holding, standard care). The main comparison of interest is between the hand massage and standard care group and the difference in means pre- and immediately posttreatment.

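### The stated 80% power does not hold for massage versus standard care after the third session: 24 patients per arm give about 72%

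*Protocol article*

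**What the plan says.** The Sample Size and Sampling Procedure section names one pairwise comparison. The trial is "powered to be able to detect a difference in the pain intensity score of 1.5 between the hand massage and standard care group". On the spread, it says: "The standard deviation of pain intensity scores is approximately a 2.0 value, which was selected for the sample size calculation". The time point, error rate and power are given as "immediately after the third massage with a 2-sided significance level of .05 and power of .80 with equal allocation to 3 arms". The calculation was done in G*Power as a repeated-measures, between-factors problem with 3 measurements, and the result is that it "would require a minimum of 72 patients". A 10% drop-out allowance raises the total to 79. No effect size f and no correlation between measurements is given.

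The Data Analysis section plans a repeated-measures ANOVA (treatment, time, interaction) for each intervention session, and then says: "The main comparison of interest is between the hand massage and standard care group and the difference in means pre- and immediately posttreatment". The Primary Outcome section likewise defines the metric as change from the pre-intervention score.

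**The concern.** The paragraph attaches 80% power to a comparison of two arms at one time, but describes a calculation for three arms and three measurements. A three-arm F test and a two-arm contrast are different tests, and a sample size found for one does not carry its power over to the other. If 72 was found for the omnibus test, the power quoted for massage versus standard care is not the power of that comparison.

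This is the main comparison on the primary outcome. If its type II error is nearer 28% than the stated 20%, a non-significant result would be read as stronger evidence against a 1.5-point benefit than it is.

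**Working it through.** **Inputs from the article.** Difference 1.5; SD of scores 2.0; two-sided 5% level; three equal arms; N = 72, so 72/3 = 24 per arm. Standardised difference d = 1.5/2.0 = 0.75.

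**Input not in the article.** The correlation between repeated scores (ρ or r below) is assumed and varied.

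**1. Reproducing 72.** For a between-groups F test with k = 3 groups and m measurements, the noncentrality is λ = f²·N·m / (1 + (m − 1)ρ), with k − 1 = 2 and N − k = 69 degrees of freedom.

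- Repeated-measures version: assumed means 0, 0.75 and 1.5 with SD 2.0 give f = 0.306 (f² = 0.09375). With m = 3 and ρ = 0.5, λ = 0.09375 × 72 × 3/2 = 10.125 and power is 0.802. At N = 69 it is 0.784, so 72 is the smallest balanced total. The result depends on ρ: the same test needs 66 at ρ = 0.4 and 81 at ρ = 0.6.
- One-way version, single measurement: f = d/2 = 0.375 gives λ = 0.140625 × 72 = 10.125, and again power 0.802.

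Two routes therefore reach exactly 72. Both are omnibus tests of three arms.

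**2. The named contrast.** Two-sample t test with noncentrality d·√(n/2). At n = 24 this is 0.75 × √12 = 2.598, with 46 degrees of freedom and critical value 2.013.

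| Patients per arm | Power for 1.5 points, SD 2.0 |
|---|---|
| 24 (N = 72) | 0.720 (0.726 with error pooled over three arms) |
| 26 (about 79/3) | 0.756 |
| 28 | 0.787 |
| 29 (N = 87) | 0.801 |

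With 24 per arm, 80% power is reached at a difference of about 1.65 points.

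**3. The change metric.** With equal variances before and after, SD of change = 2.0·√(2(1 − r)). Taking 1.5 as the difference in mean change, at 24 per arm:

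| r | SD of change | Power |
|---|---|---|
| 0.3 | 2.37 | 0.58 |
| 0.5 | 2.00 | 0.72 |
| 0.6 | 1.79 | 0.81 |
| 0.7 | 1.55 | 0.91 |

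The 80% line is crossed at r of about 0.59.

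**4. A baseline-adjusted contrast (ANCOVA).** Residual SD = 2.0·√(1 − r²), with 45 degrees of freedom. At 24 per arm, power is 0.76 at r = 0.3, 0.84 at r = 0.5 and 0.89 at r = 0.6.

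**The case against.** The strongest reply is that 72% belongs to an unadjusted comparison of post-session scores, whereas the article's own metric is pre-to-post change. That is fair. On that metric the power may lie above or below 80%, and from a correlation of about 0.6 the stated figure is met. But the article gives no correlation, its SD is explicitly for scores, and the sample-size paragraph fixes a difference at one time point. At r = 0.5, the value that reproduces 72 by the repeated-measures route, change-score power is again 72%.

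It can also be said that the practical loss is small. The detectable difference moves from 1.5 to about 1.65, still under the 2 points the article treats as clinically significant, and power for 2 points at 24 per arm is 0.92. This stands, and it is why rewording is enough.

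Two stronger readings are tempting, and the article does not support them.

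- A reader might infer that the planned treatment main effect is badly diluted because no difference between arms can exist at the score taken before the intervention. But randomization precedes the first session and the analysis is run per session. The score before the third session therefore follows two earlier sessions, and a difference may already exist there. Nor does the sample-size paragraph say which 3 measurements it means.
- A reader might infer that 72 certainly came from an omnibus test averaged over repeated measurements. The one-way route gives the same number without any averaging, so the exact origin is unknown.

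**Conclusion.** The power is misstated for the comparison to which it is attached. For massage versus standard care immediately after the third session, with 1.5 points, SD 2.0 and a two-sided 5% test, it is about 72% at 24 per arm and about 76% with all 79 evaluable, not 80%. This rests only on inputs the article states, plus an unadjusted two-sample comparison. It does not depend on how 72 was obtained.

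The number 72 is not shown to be an arithmetical slip: it is consistent with a three-arm omnibus test, and that attribution is an inference. Nor can it be said that the trial must miss 80% under every analysis. On the change metric the answer runs from 0.58 to 0.91 over correlations of 0.3 to 0.7, and the article does not say where in that range it expects to be.

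**What to change.** In the sample-size paragraph, replace the 80% statement with the power of the massage-versus-standard-care contrast: about 72% for 1.5 points at 24 evaluable per arm (about 76% if all 79 are evaluable), or equivalently 80% for about 1.65 points. If change from the pre-intervention score is to be the metric, state the assumed correlation and the power that follows from it. If the three-arm calculation is kept, give its f and correlation and say that it concerns the omnibus test.

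Preferably, also name as the primary test an ANCOVA contrast of massage versus standard care on pain immediately after the third session, adjusted for the pain score before the first intervention. That score precedes any treatment, so adjusting for it does not remove an effect carried over from the first two sessions. Its power should be given over a range of assumed correlations (0.76, 0.84 and 0.89 at 0.3, 0.5 and 0.6), because the article offers no value for scores about a day apart.

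No extra patients are needed. The cost is rewording and, unless the adjusted analysis is adopted and the correlation proves adequate, a less favourable stated power. The article reports 24 patients randomized so far, so the change can be made before the analysis.

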### Randomization

Before the study begins, permuted-block randomization will be generated for 85 patients by a statistician using SAS computer software (SAS Institute) and block sizes of 3, an allocation ratio of 1:1:1, and one strata to minimize the imbalance in the number allocated to each group. Then, the randomization schedule will be transcribed in sequentially numbered and opaque sealed envelopes by a research coordinator not involved in assignment allocation to ensure allocation concealment. The allocation list will be stored in a locked filing cabinet of the principal investigator and will not made accessible to the interventionist involved in enrollment and treatment allocation.

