## Results

Recruitment started the end of April 2016, and to date 34 patients have already been recruited. Of these, 24 patients were randomized and had data collection done as several were medically unstable postoperatively or had their surgery cancelled/postponed. Data collection is expected to be complete by January 2017.

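### The total of 79 falls one patient short of the stated 10% drop-out allowance on 72: 72/0.90 is 80, a slip worth under one percentage point of power

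*Protocol article*

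**What the plan says.** The section Sample Size and Sampling Procedure builds the total in three steps.

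- The target effect: "To detect a mean difference in pain intensity scores of 1.5 points (SD 2.0) immediately after the third massage". The test is two-sided at .05, the power is .80, the three arms are equal in size, and treatment is the between-patient factor in a model for three repeated measurements.
- The size before drop-out: this "would require a minimum of 72 patients".
- The allowance for loss: "a 10% drop-out rate is considered in the calculation of the total sample size". The section supports it with cited attrition of 0% in three studies and 35/287 (12.2%) in a fourth. It then concludes: "Therefore, the final size required for this RCT is 79".

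Two other places bear on the total. The abstract repeats it ("A total of 79 patients who are 18 years or older") and says that these patients will be recruited and then allocated 1:1:1. The Randomization section says that "permuted-block randomization will be generated for 85 patients", in blocks of 3.

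**The concern.** The article presents 79 as the consequence of a minimum of 72 and a 10% loss. If 10% of 79 patients are lost, fewer than 72 remain, so the total does not do what the text says it does. The likely cause is a common shortcut, adding 10% of the evaluable number instead of dividing by the retained fraction, followed by rounding a required minimum down.

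What is at stake is the accuracy of a figure against which the trial will be reported. A reader who checks the calculation will find that its last step fails. The consequence for the trial's ability to detect the planned effect is very small, as the next section shows.

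**Working it through.** **Inputs, all from Sample Size and Sampling Procedure.** Evaluable minimum 72; drop-out 10%; stated total 79; difference 1.5; SD 2.0; two-sided alpha .05; power .80; three arms; three measurements. The minimum of 72 is taken as given here.

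**Step 1: reproduce 79.** 72 × (1 + 0.10) = 79.2. Rounded down, this is 79. Rounded up, as a minimum should be, it is 80.

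**Step 2: the size that covers a 10% loss.** N = 72 / (1 − 0.10) = 80.0. Both conventions therefore give 80.

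**Step 3: what each total leaves after a 10% loss.**

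| Randomised | × 0.90 | Against 72 |
|---|---|---|
| 79 | 71.1 | 0.9 short |
| 80 | 72.0 | met |
| 81 (27 per arm) | 72.9 | met |

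**Step 4: the loss that 79 does cover.** 1 − 72/79 = 7/79 = 0.0886, or 8.9%.

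**Step 5: the cost in power.** This needs a model that gives 72. The article does not state the correlation between repeated measurements or where the hand-holding mean lies. Two assumptions reproduce the figure: correlation 0.5, and the hand-holding mean halfway between the other two.

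- Effect size: f = √[(1.5/2.0)² / 6] = √0.09375 = 0.306.
- Noncentrality: λ = f² × N × 3 / (1 + 2 × 0.5) = 0.140625 × N, with 2 and N − 3 degrees of freedom.
- The smallest N with power of at least .80 is 72, which matches the article.

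| Patients analysed | λ | Power |
|---|---|---|
| 71 | 9.98 | 0.796 |
| 72 | 10.13 | 0.802 |

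The difference is about 0.6 percentage points.

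**Step 6: room on the randomisation list.** The list has 85 places. A total of 80 leaves 5 unused and 81 leaves 4. The latter uses exactly 81/3 = 27 complete blocks.

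**The case against.** The strongest reply is that the shortfall is immaterial. It is one patient. The 10% is a rounded planning figure chosen between observed rates of 0% and 12.2%, and the gap between 8.9% and 10% lies well inside that spread. The article also plans to keep collecting data after an intervention is stopped (Criteria for Modifying Interventions), which should limit missing outcomes. All of this stands, and it is why the point is minor. It does not make the sentence correct: the article gives an exact minimum and an exact rate, and its total does not satisfy them.

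Three stronger readings are tempting, and the article does not support them.

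- *79 counts consented patients.* The abstract says that 79 will be recruited, and the Results section uses that word for an earlier stage: "to date 34 patients have already been recruited. Of these, 24 patients were randomized". A reader might apply 24/34 (71%) to 79 and infer that only about 56 would be randomised. But the abstract describes the 79 as patients who have already had surgery, and its next sentence says that they will be randomly allocated. The 34 include patients whose surgery was cancelled or postponed, so they are a different group. A list for 85 also fits 79 randomised. The word is used loosely; the target is not in doubt.
- *79 cannot be allocated 1:1:1.* It is not a multiple of 3, but blocks of 3 would simply give 27, 26 and 26. The allocation ratio does not require a divisible total.
- *The list of 85 is faulty.* It amounts to 28 full blocks and one extra place (28 × 3 + 1 = 85). Every total considered here is reached before that last place, so nothing follows from it.

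**Conclusion.** The point holds as a minor arithmetic error. Given 72 and 10%, the total should be 80, and 79 is one short. It leaves 71.1 patients after the stated loss and covers 8.9%.

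The shortfall of 0.9 patients and the 8.9% rest only on the article's own figures. The power figures (about 0.796 against 0.802) also rest on the assumed correlation of 0.5 and the assumed halfway position of the middle arm. The error does not threaten the design, the analysis or the conclusions, and it gives no ground for predicting an underpowered trial.

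**What to change.** Make one of two changes in Sample Size and Sampling Procedure, and carry it into the abstract.

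- Keep 79 and state that it allows for 8.9% loss. This costs a few words and no patients.
- State the target as 80 randomised, or 81 if equal arms of 27 are wanted. This costs one or two more patients and needs no change to the randomisation list. The Results section reports 24 randomised so far, so the target can still be restated before recruitment ends.

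As an optional wording point, the abstract could say *randomized* instead of *recruited* for this total, so that the word has one meaning throughout the article.
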